## Abstract

**Background:**

COVID-19 can lead to increased psychological symptoms such as post-traumatic stress disorder (PTSD), depression, and anxiety among patients with COVID-19. Based on the previous mindfulness-based interventions proved to be effective, this protocol reports a design of a randomized controlled trial aiming to explore the efficacy and possible mechanism of a mindful living with challenge (MLWC) intervention developed for COVID-19 survivors in alleviating their psychological problems caused by both the disease and the pandemic.

**Methods:**

In April 2021, more than 1600 eligible participants from Hubei Province of China will be assigned 1:1 to an online MLWC intervention group or a waitlist control group. All participants will be asked to complete online questionnaires at baseline, post-program, and 3-month follow-up. The differences of mental health status (e.g. PTSD) and physical symptoms including fatigue and sleeplessness between the COVID-19 survivors who receiving the online MLWC intervention and the control group will be assessed. In addition, the possible mediators and moderators of the link between the MLWC intervention and target outcomes will be evaluated by related verified scales, such as the Five Facets Mindfulness Questionnaire. Data will be analyzed based on an intention-to-treat approach, and SPSS software will be used to perform statistical analysis.

**Discussion:**

The efficacy and potential mechanism of MLWC intervention in improving the quality of life and psychological status of COVID-19 survivors in China are expected to be reported. Findings from this study will shed light on a novel and feasible model in improving the psychological well-being of people during such public health emergencies.

*Trial registration* Chinese Clinical Trial Registry (ChiCTR), ChiCTR2000037524; Registered on August 29, 2020, http://www.chictr.org.cn/showproj.aspx?proj=60034.
[figure not shown]

## Background

Coronavirus disease 2019 (COVID-19), the infection caused by severe acute respiratory syndrome coronavirus 2 (SARS-CoV-2), was first reported on December 31, 2019. On March 11, 2020, the World Health Organization (WHO) declared the COVID-19 as a pandemic due to its rapid global spreading. Globally, there have been 122 536 880 COVID-19 cases and 2 703 780 deaths, particularly among vulnerable populations such as patients with chronic diseases and the elderly [1, 2]. As of 24:00 pm on March 22, 2021, China alone has resulted in 102 566 cases and 4850 deaths due to COVID-19 [3]. It can be seen that the mortality rate of COVID-19 has been declining recently, which means that more and more patients have been released from the hospital after being cured. Therefore, the focus has now been shifted to taking measures to rehabilitate COVID-19 survivors, including the restoration of their physical functions and psychological development.

Evidence suggests that this disease has psychological consequences on healthcare workers, students, psychiatric patients and general workers, especially for COVID-19 patients [4–13]. Immediately after the outbreak, a considerable proportion of patients with COVID-19 reported post-traumatic stress disorder (PTSD) (more than 33.0%), depression (60.2%), and anxiety (55.3%) symptoms in Shanghai, China [9]. In addition, a survey conducted in March, 2020 showed that 45.9% of patients had symptoms of depression, 38.8% had anxiety and 54.1% had insomnia in Wuhan, China [10]. COVID-19 survivors in other countries have similar psychological status [11–13]. In Ecuador, one of the most affected countries by the COVID-19 pandemic in Latin America, of the 759 confirmed or suspected COVID-19 patients, 20.3% showed moderate to severe depressive symptoms, while 22.5% showed moderate to severe anxiety [11]. In addition, 22.6% and 16.3% of respondents reported clinically concerning levels of psychological impact in Vietnam and the Philippines, the Asian countries with similar cultural context as China [12, 13]. Over time, while the mental symptoms and quality of life of COVID-19 survivors might improve in a certain extent, they are still significantly worse when compared to the rest of the population who did not suffer from COVID-19. Therefore, the psychological impacts of COVID-19 should not be overlooked and should be investigated from the long-term public health perspectives.

In view of the current epidemic situation and the corresponding prevention and control requirements, internet-based interventions can provide an alternative to face-to-face therapy in enhancing mental health and quality of life for patients with COVID-19. Internet-based healthcare has enabled patients with a variety of geographical distance to receive the same therapy and get benefits from the same interventions, such as digital cognitive behavioural therapy for insomnia [14–16]. This form of psychotherapy can provide treatment and intervention efficiently to patients under the requirements of social distancing during the COVID-19 epidemic [14]. Mindfulness-based intervention (MBI) is an approach that focuses on the cultivation of conscious awareness, and orientation towards the present moment with curiosity and openness, which has been shown helpful in the treatment of mental health [17–20]. Unlike behavioral therapy, which involves relaxation techniques and changing the schedule of daily activities, mindfulness-based interventions help patients cope with anxiety and depression by enhancing their ability to manage stress and reducing negative coping behaviors, hence are more adaptive and persistent [20]. Especially when combined with the web-based technology, mindfulness-based intervention can benefit patients who are infected and treated in isolation wards, and those who are quarantined with no access to psychotherapy as well. [17, 20] An internet-based integrated intervention including some mindfulness skills on depression and anxiety symptoms in Chinese patients with COVID-19 has demonstrated that patients of the intervention group exhibited significantly decreased levels of depression and anxiety symptoms in comparison with those of the control group over a 2-week study period [18].

In the mainland of China, WeChat App and its small programs have dominated the browsing time of mobile phone users [21] Given the emerging need for psychological rehabilitation among COVID-19 survivors recently, this randomized controlled trial will be conducted in this population to examine the effectiveness and feasibility of a 6-week Mindful Living With Challenge (MLWC) intervention focusing on mental health and quality of life via WeChat. We hypothesized that the training could enhance the physical and mental health at post-program and 3-month follow-up.

## Methods/design

### Study design

This is a prospective, randomized, parallel-group, double-blind, blank controlled trial involving an online 6-week MLWC intervention with a 3-month follow-up. More than 1600 COVID-19 survivors over 18 years old will be randomized to: (1) intervention group: this group will receive a baseline questionnaire followed by a 6-week web-based MLWC intervention, and two questionnaire surveys at post-program and 3 months after the intervention, or (2) waitlist control group: participants in this group will receive three questionnaire surveys conducted simultaneously with the intervention group, and start the same intervention after a 3-month waitlist period (Fig. 1). This study protocol is reported in accordance with SPIRIT reporting guidelines [22]

**Fig. 1 Fig1:**
[figure not shown]
Flow chart of the protocol. MLWC: Mindful living with challenge; ITT: Intention-To-Treat

### Study objectives

The primary study objective of this study is to assess the efficacy of the MLWC intervention on PTSD, depression, and anxiety among COVID-19 survivors. The secondary study objective is to investigate the effects of the MLWC intervention on fatigue and sleep quality among COVID-19 survivors. The exploratory objective is to determine how mindfulness training affects mental health and quality of life among COVID-19 survivors and to evaluate the possible mediators and moderators (mindfulness, stillness, nonattachment, resilience and perceived social support) of the link between the MLWC intervention and target outcomes.

### Settings

The study will be carried out at the Hubei Provincial Hospital of Integrated Traditional Chinese and Western Medicine, Hubei Province, China. All researchers and support staff in this project will be trained based on the same protocol and are required to have an educational background in medicine or public health. Digital informed consent will be obtained from all subjects to ensure their voluntary participation. This study is planned to be performed in April 2021 and will last for about 4 months (The study has not been carried out before the submission).

### Sample size

A priori power analysis has been conducted on the statistical software G*Power 3.1.9.2 (Heinrich-Heine-Universität Düsseldorf). The trial between the MLWC intervention group and the control group will be tested superiority in promoting mental health status at a superiority margin of 10%. Thus, with a 1:1 allocation to each group and allowing for a 40% attrition rate, at least 1600 participants will be recruited (power = 0.9, α = 0.05, two-tail).

### Recruitment

Participants will be recruited through advertisements posted in hospitals and publicity by doctors in outpatient clinics or patient contact groups. Interested participants will be informed about the benefits and possible risks of participation in the study, including failure to achieve the expected intervention effects. Completion of electronic informed consent will be required before screening the eligibility of participating in the study.

Once the informed consent is obtained, a trained research staff will complete the eligibility checklists and record the candidates who fail to meet the inclusion criteria. Furthermore, a senior nurse will record the mobile phone number of participants to facilitate follow-up services. All of the above personal information will be kept confidential on an encrypted laptop and used for research purposes only. Table 1 shows schedule of enrolment, interventions and assessments.

**Table 1 Tab1:** Schedule of enrolment, interventions, and assessments

Study period						
	Enrolment	Allocation	Post-allocation			Close-out
Time point	0	t_0_	t_1 baseline_	t_2 Intervention period_	t_3 Post-assessment_	t_4 Follow-up assessment_
*Enrolment*						
Eligibility screen	X					
Informed consent	X					
Allocation		X				
*Interventions*						
The Mindful Living with Challenge intervention group				X		
Waitlist control group				X		
*Assessments*						
Primary outcome measures						
Impact of Events Scale-Revised			X		X	X
Patient Health Questionnaire			X		X	X
Generalized Anxiety Disorder Questionnaire			X		X	X
Peace of Mind Scale			X		X	X
Secondary outcome measures						
Fatigue Scale-14			X		X	X
Pittsburgh Sleep Quality Index			X		X	X
The possible mediators and moderators						
Five Facets Mindfulness Questionnaire			X		X	X
The Nonattachment Scale			X		X	X
The Stillness Scale			X		X	X
The Resilience Style Questionnaire			X		X	X
The Social Support Scale			X		X	X

‘X’ represents the research procedure or content involved in each time point

### Eligibility criteria

#### Inclusion criteria

Participants must first agree to the electronic informed consent in order to participate in the study as required by the ethics committee. The participants have to meet the following criteria:Over 18 and under 65 years oldHave a history of COVID-19 infectionProficiency in ChineseBe able to independently cooperate with doctors to complete various scale assessmentsHave a mobile communication equipment such as a mobile phone, and a WeChat account.Mobile equipment can access the internet at any timeHave not received medications for PTSD, depression, anxiety, fatigue, or sleep disorders within 1 month prior to enrollment in the study.

#### Exclusion criteria

Those who meet any of the below criteria will be excluded:Have serious cognitive impairment.Have serious heart, brain, lung, kidney, liver, and other medical diseases or tumors.Difficult to cooperate with the questionnaire survey and intervention.

### Randomization and blinding

Participants who meet the eligibility criteria will be randomly assigned (in a 1:1 ratio) to the online MLWC intervention group or waitlist control group. They are supposed to provide informed consent by clicking the ‘I agree to join in the research’ button on the electronic details page of the study. After that, a Quick Response (QR) code will pop up on the page. By scanning this code, participants will be randomly assigned to the intervention or control group (in a 1:1 ratio) by computer-generated numbers. The trial will blind all people who might influence the outcome assessments, including the participants, data analysts, and outcome assessors. Before the trial, the principal investigator of the project will organize training on the randomization procedure and ensure that each research staff is clearly aware of their responsibilities.

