### Data collection, management, and monitoring

Data will be collected at baseline (one week before the intervention), post-intervention (one week after the last session of MLWC), and at 3-month of follow-up. The questionnaire comprises structured and open-ended questions about mental health status, quality of life, and satisfaction with the program. Demographics will be collected at baseline, including age, employment status, education level, marital status, and other information.

Electronic questionnaires powered by the REDCap software will be used to collect data, hence there will be no formal data monitoring committee. Survey questions filled up by the participants will be automatically uploaded to the read-only web-based database to ensure the authenticity of the data. Moreover, our researchers will promptly check the collected data after each questionnaire survey.

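### Table 1 schedules the self-reported baseline after allocation in a waitlist trial, and the order of consent, screening and randomisation is described in two ways

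*Protocol article*

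**What the plan says.** **Baseline.** Table 1 (Recruitment section) lists eligibility screening and consent at enrolment, allocation at t0, and all outcome, mediator and moderator scales first at t1, which sits under the post-allocation heading. Study design describes people being randomised to an arm and says of the intervention arm: "this group will receive a baseline questionnaire followed by a 6-week web-based MLWC intervention". The data collection section gives only the timing relative to the course: "Data will be collected at baseline (one week before the intervention".

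**Arm knowledge.** Randomization and blinding states: "The trial will blind all people who might influence the outcome assessments, including the participants, data analysts, and outcome assessors". Under Study design, control participants are to "start the same intervention after a 3-month waitlist period". The Intervention section has the intervention arm join the WeChat program through a QR code scan and then receive the course.

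**Screening.** Recruitment says: "Completion of electronic informed consent will be required before screening the eligibility of participating in the study", and then that "a trained research staff will complete the eligibility checklists and record the candidates who fail to meet the inclusion criteria". Randomization and blinding opens with the restriction "Participants who meet the eligibility criteria will be randomly assigned (in a 1:1 ratio", moves to the consent click, and continues: "After that, a Quick Response (QR) code will pop up on the page. By scanning this code, participants will be randomly assigned".

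**Use of baseline.** The Statistical analysis section plans t-tests and chi-square tests of baseline differences, repeated measures ANOVA on the six instruments and paired t-tests within arms.

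**The concern.** A baseline measured after allocation is safe only if the participant does not yet know the arm. All the scales here are self-reported, and one arm is offered a course while the other is asked to wait. If the arm is known, hope or disappointment can move the baseline answers, and people unhappy with their arm can leave the form unfinished. Baseline then becomes a post-randomisation variable: an imbalance in it may be an effect of allocation rather than chance, and any contrast that subtracts it carries the shift into the treatment effect.

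The second issue is procedural. Two sections each describe what follows consent, and they name different steps. Staff building the electronic pages could not tell from the article what must be complete before the randomising code appears.

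**Working it through.** **1. Where baseline sits relative to allocation.**
- Table 1: t0 is allocation and t1 is baseline. The numbering and the column heading both put baseline second.
- Study design: randomisation to an arm, then a list of what that arm receives, beginning with the baseline questionnaire. This is consistent with Table 1 but would not fix the order by itself.
- Data collection: one week before the course. This is compatible with baseline before or after allocation.
- Randomization and blinding: no baseline form is mentioned before the QR scan.

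Table 1 is therefore the firm evidence, and no section places baseline first.

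**2. Whether the arm is known at t1.** No section says when the arm is disclosed. Blinding of participants is asserted. Against that, a participant either gets access to a course or does not, and the intervention arm enters the program by QR scan; the article does not say whether this is the same code as the randomising one. No step is described that hides the arm until the baseline form is submitted. Knowledge of the arm is thus likely but inferred.

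**3. Size, as an illustration only.** The documents give no figure for such a shift. Inputs:
- From the Sample size section: 1600 recruited and 40% attrition, so 1600 × 0.6 / 2 = 480 completers per arm.
- Assumed: no true effect; one arm's baseline mean shifted by b = 0.05, 0.10 or 0.20 SD; a fraction k of the shift still present at the later survey; pre-post correlation ρ of 0.5 to 0.7; normal approximation; a single later time point.

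Bias of the change-from-baseline contrast, in absolute size = b(1 − k).
- k = 0 (shift at baseline only): 0.05, 0.10, 0.20 SD.
- k = 0.5: 0.025, 0.05, 0.10 SD.
- k = 1: zero.

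Standard error of the contrast = √(2(1 − ρ) × 2/480).
- ρ = 0.5: √(2/480) = 0.0645.
- ρ = 0.7: √(1.2/480) = 0.0500.

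Two-sided type I error at k = 0 = Φ(−1.96 + b/SE) + Φ(−1.96 − b/SE), against a nominal 5%:

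| b (SD) | ρ = 0.5 | ρ = 0.7 |
|---|---|---|
| 0.05 | 12.1% | 17.0% |
| 0.10 | 34.1% | 51.6% |
| 0.20 | 87.3% | 97.9% |

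A baseline-adjusted analysis, which the article does not name, would have bias ρb: from 0.5 × 0.05 = 0.025 SD to 0.7 × 0.20 = 0.14 SD. Adjustment reduces the problem but does not remove it.

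The sign is not fixed. On a symptom scale, hope that lowers the intervention arm's baseline makes its improvement look smaller; over-reporting of symptoms in that arm would make it look larger.

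**4. Screening sequence.**
- Recruitment: consent, then staff checklist.
- Randomization and blinding: eligible participants, then consent click, then QR code, then allocation.
- Table 1: screening and consent both at enrolment, before allocation.

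All three agree that screening should precede allocation. They differ on whether it precedes or follows consent, and the QR mechanism shows no step that holds the code back until the checklist is passed.

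**The case against.** The article says participants are blinded, and the arm might be revealed only when the course opens, after baseline is complete. That is possible, so it would be wrong to state as fact that participants know their arm at t1. But no such concealment is described, and blinding of participants is hard to credit with a waitlist control.

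Fig. 1 is not visible here, and Study design may simply list each arm's assessments without fixing their order. Both points are fair; they leave Table 1 as the main support, and Table 1 is explicit.

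A reader might infer from the QR sentence that unscreened people can be randomised and would later have to be excluded, breaking intention-to-treat. The documents do not support this. The same section restricts randomisation to people who meet the criteria, Table 1 puts the screen at enrolment, and nothing provides for exclusion after randomisation. What remains is an unreconciled sequence.

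A reader might also want to express the bias as a share of the difference the trial can detect. The Sample size section gives a 10% margin and no SD, so the article offers no standardised effect for that. The shift itself is assumed, and it shrinks or cancels in a change contrast if it persists at later surveys.

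**Conclusion.** The point holds in this form. The published schedule takes self-reported baseline scores after allocation in a waitlist trial, and the planned balance tests, repeated measures ANOVA and paired t-tests use those scores. The harm depends on participants knowing their arm when they complete the form, which is a reasonable inference and not something the article states. If they do know it, a shift of 0.05 to 0.20 SD confined to baseline gives an equal bias in a change-from-baseline contrast, in an unknown direction, and a smaller one if the shift lasts. These are assumed values, not estimates. Once collected, a baseline affected in this way cannot be restored by analysis.

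Separately, the Recruitment and the Randomization and blinding sections need reconciling on where screening falls. This is a gap in the described mechanism, not evidence that ineligible people would be enrolled.

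**What to change.** In Table 1, move the baseline assessment ahead of allocation. In Randomization and blinding, state that the QR code is released only after the eligibility checklist is passed and the baseline questionnaire is submitted, so that the order is consent, screening, baseline, allocation. Align the Recruitment and Study design sections with that order.

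The cost is a reordering of electronic pages and one table. A few people who do not finish the baseline form will not be randomised.

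If enrolment has already followed the published order, report when participants learned their arm relative to the baseline form, and give baseline completion by arm.

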### Intervention

#### The mindful living with challenge (MLWC) intervention

Participants in the intervention group are required to follow the developed WeChat small program by scanning the QR code, and then receive the online MLWC intervention. The MLWC intervention will be developed by two psychiatrists, and one of them has been certified in the Training of Mindfulness Facilitation program at the Mindful Awareness Research Center of University of California, Los Angeles (UCLA). The MLWC intervention adopts some elements from mindfulness-based stress reduction and Mindful Awareness Practices, and includes mindfulness meditation and mindful stretching as core components. A similar intervention has been successfully used on attention monitoring and acceptance in pregnant women in China [19]. Through a series of mindfulness training courses, participants are hypothesized to increase their ability to regulate their emotions and learn to observe the physical pain and psychological frustration caused by COVID-19 infection with equanimity. The purpose of the study is to help participants improve their skills in coping with psychological symptoms, improve their quality of life during recovery, and prepare to return to a normal life.

The MLWC intervention will involve internet-based mindfulness training conducted in six weekly courses of two sessions a week and 0.5 h per session, which focus on the four important parts of MBI: attention control, self-awareness, acceptance and discernment, and relating to difficult thoughts/emotions. Two new sessions of online lessons will be updated weekly in six weeks. The study participants are expected to spend an average of 1 h per week viewing each lesson, which consisted of a theoretical instrument, some meditation practices, and homework in the form of audio and video. Participants will be required to perform formal/informal mindfulness practice at home for 5 min daily initially, advancing to 20 min daily at the end of the intervention period, and to record or report their difficulties and progress during the practice. To enhance adherence, push notifications from the WeChat small program will be sent to participants daily to remind them about their weekly attendance and regular practice. See Table 2 for the context of the MLWC intervention.

**Table 2 Tab2:** The content of mindful living with challenge (MLWC) intervention

Session	Theoretical instrument	Meditation practice	Homework

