#### Control group

Participants in the waitlist control group will receive the full 12-session online MLWC intervention upon completion of all treatment procedures by the intervention group after the 3-month follow-up survey.

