Although previous studies showed that face-to face mindfulness practices are effective to alleviate mental and physical symptoms including depression and sleeplessness [17–19, 45], the web-based mindfulness intervention were proved to have potential in improving the mental health of various study population with more feasibility and acceptability [46]. Currently, the WeChat App and its small programs have become an integral part of everyday life for the majority of the population in China [21]. To ensure the efficacy and the quality of the mindfulness intervention, the content of the intervention course will be developed by a team with clinical psychology background and delivered by a psychiatrist with mindfulness training qualification. Also, to enhance the adherence of the mindfulness-based intervention, professionals in information technology will design the specific small program for managing the questionnaire collection and distribution of the embedded video and audio courses during the study period.

The evaluation of the online MLWC intervention proposed in this study for the treatment of psychological symptoms among COVID-19 survivors is scarce in the international literature. The current study will use RCT, double-blind, evidence-based meditation design, and a longer period of intervention and follow-up, which may ensure more solid conclusions compared to similar studies [18, 47]. Moreover, since some studies have found that the mindfulness intervention did not affect all of the mindfulness facets [48, 49], we will explore 12 sessions of the MLWC intervention as intermediaries on the outcome measures, to determine which sessions have the greatest impact on the outcome, and provide more solid evidence for future psychological interventions. Furthermore, given the inexpensive and portable features of the online MLWC intervention, it can be more easily implemented in harder-to-reach but internet-accessible populations. However, it should be noted that, this study will mainly use questionnaires to measure psychiatric symptoms and do not make clinical diagnosis through structured clinical interview and functional neuroimaging, which may result in measurements that are inconsistent with clinical examinations [50, 51].

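### The article claims double-blinding with blinded participants and outcome assessors, but a waitlist design with self-completed outcomes allows only the data analysts to be masked

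*Protocol article*

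**What the plan says.** Three sections of the protocol article claim blinding.

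- **Study design** describes a "randomized, parallel-group, double-blind, blank controlled trial".
- **Randomization and blinding** names who is blinded: "The trial will blind all people who might influence the outcome assessments, including the participants, data analysts, and outcome assessors".
- **Discussion** counts blinding among the trial's merits: "The current study will use RCT, double-blind, evidence-based meditation design". Together with the longer intervention and follow-up, these features are said to offer the prospect of firmer conclusions than similar studies.

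Other sections describe what each arm experiences.

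- **Intervention:** six weekly courses of two sessions each, home practice rising from 5 to 20 minutes a day, and reminders: "push notifications from the WeChat small program will be sent to participants daily to remind them about their weekly attendance and regular practice".
- **Study design**, on the control arm: its participants answer the same three surveys and "start the same intervention after a 3-month waitlist period".
- **Control group**, on timing: "Participants in the waitlist control group will receive the full 12-session online MLWC intervention upon completion of all treatment procedures by the intervention group", which that section places after the 3-month follow-up survey.
- **Recruitment:** "Interested participants will be informed about the benefits and possible risks of participation in the study", including the possibility that the intervention does not work as hoped.

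On measurement, Outcome measurements lists questionnaire scales for every primary and secondary outcome. Data collection, management, and monitoring has participants complete them electronically. The Discussion says that no structured clinical interview is used.

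**The concern.** Blinding of participants and assessors is meant to stop knowledge of the arm from colouring the outcome. Here the outcomes are self-rated distress, peace of mind, fatigue and sleep, which expectation in one arm or disappointment in the other can affect directly. If the label is taken at face value, a reader will judge the risk of bias in the primary outcomes as lower than it is. The same reader will credit any difference to the mindfulness training itself, although the design cannot separate that from the effect of knowing one has been given a course or told to wait.

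This is not a detail that a fuller protocol or an analysis plan could supply. The article makes a positive statement that its own design contradicts.

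**Working it through.** **Step 1. Set each claim against the design.**

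| Group said to be blinded | What the article describes | Can it hold? |
|---|---|---|
| Participants | 6 × 2 = 12 sessions, daily practice and daily reminders in one arm; surveys only in the other; the control is called blank; no sham, attention control or concealment of the study aim | No |
| Outcome assessors | Scales completed electronically by participants; no structured interview; no independent rater described | No: the assessor is the participant |
| Data analysts | Nothing in the design reveals the arm to an analyst who works from coded labels | Yes, if coding is done |

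The contrast between the arms is in place at the post-program survey. By the Control group section it remains in place at the 3-month survey, so both post-baseline assessments are affected.

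**Step 2. Check whether another passage rescues the claim.** The Inclusion criteria mention working with doctors on scale assessments. That is a requirement about the participant's ability. It does not describe a rater who is independent of the participant or unaware of the arm, and the data collection section has participants entering their own answers. The limitations sentence in the Discussion deals only with questionnaires as against clinical diagnosis and says nothing about blinding.

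**Step 3. Illustrate the size.** The plan has no figure of its own to reproduce here, and every input to the calculation is an assumption or follows from one:

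- Completers per arm: 1600 × (1 − 0.40) / 2 = 480, taking the recruitment target and attrition allowance in Sample size as realised.
- Test: a two-sided two-sample comparison of means at 0.05 on one scale.
- True effect: zero.
- Reporting bias b in SD units: 0.05, 0.10 and 0.20. The article gives no value.

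The standard error of the difference in SD units is √(2/480) = 0.0645. The chance of P < 0.05 in favour of the intervention is Φ(b/0.0645 − 1.96).

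| b (SD) | b / 0.0645 | Chance of P < 0.05 |
|---|---|---|
| 0.05 | 0.77 | about 12% |
| 0.10 | 1.55 | about 34% |
| 0.20 | 3.10 | about 87% |

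With no bias, the two-sided chance is 5%.

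**The case against.** The other side has several fair points.

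- **A waitlist comparator is a legitimate choice.** This stands. The point concerns the description of the design and does not ask for a different control arm.
- **Correcting the words leaves any bias unchanged.** This also stands. The percentages above show why the label matters. They do not measure what the correction achieves, which is an accurate account of the risk of bias and of what may be concluded.
- **The illustration is not the trial's own error rate.** This is correct. Statistical analysis plans an intention-to-treat approach with repeated measures ANOVA, and the bias values are assumed. The low end, 12% at 0.05 SD, is modest.

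A reader might also infer more than the documents support.

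- *That none of the stated blinding can exist.* Analysts are on the list, and they can be masked.
- *That the bias can be set against a target effect of about 0.21 SD.* That value comes from working backwards from 480 per arm: (1.960 + 1.282) × 0.0645 = 0.209. Sample size gives only a 10% margin, with no SD, endpoint or reference rate. A two-proportion calculation with a 38.8% control rate and a 10-point reduction gives 1564, also close to 1600. No comparison with a target in SD units is therefore warranted.
- *That participants know their arm from the first day, or before the baseline survey.* Table 1 places baseline after allocation, but the article does not say when participants learn their arm. It is enough that those in the course know they are receiving it, and those without it know they are not, by the time of the post-program survey.
- *That the Discussion rests its confidence on blinding alone.* Blinding is one of several features listed, and the wording is tentative.

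**Conclusion.** The claim that participants and outcome assessors are blinded is wrong as written and should be corrected before the article is relied on. The contradiction is internal to the article and needs no outside figure. It affects every primary and secondary outcome, because all are self-completed scales. Analyst masking is the one part of the claim that the design permits.

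The size of any bias is unknown. On the assumed inputs above, a reporting bias between 0.05 and 0.20 SD with no true effect would produce a nominally significant result on a single scale in about 12% to 87% of trials. This shows that a small bias could matter at this sample size. It is not an estimate of what will happen.

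What the trial can support is a conclusion about being offered the course compared with waiting for it, with expectation effects included.

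**What to change.** 1. **Study design and Discussion:** replace the term double-blind with *open-label to participants, self-reported outcomes, masked data analysts*.
2. **Randomization and blinding:** remove participants and outcome assessors from the list of those blinded, together with the statement that everyone able to influence the outcome assessments is blinded. Keep analyst masking, and state that arm labels stay coded until the primary analysis is complete.
3. **Discussion:** stop listing blinding as a strength. Add expectation and reporting bias in self-completed outcomes to the limitations. Limit the planned conclusion to the effect of being offered the intervention against waiting, expectation effects included.

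The comparator, sample size, outcomes and analysis method do not change. The design is described less favourably, and someone outside the analysis has to hold the arm codes.
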